## 6.4 Drug Discontinuation Due to Adverse Drug Reactions

As a study outcome, drug discontinuation due to adverse drug reaction is defined when study drug(s) cannot be re-instituted safely.

Drug discontinuation for causes other than adverse drug reactions (e.g., withdrawal from study, loss to follow-up, etc), will be defined as the date the patient withdrew from the study.

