### **8.1.4 Discontinuation and Re-initiation of Antiretroviral Therapy**

#### **8.1.4.1 Definitions**

To hold study drug means to temporarily withhold the use of one or all medications. When a study drug is held, it may be re-started as clinically indicated.

To discontinue study drug means to stop one, or more, study medications without the intent of restarting the medication. It is a synonym for permanent discontinuation of treatment. A study medication may first be held during the evaluation of a patient before a decision is made to discontinue the medication.

To restart study drug means to provide again a study medication that was previously held in a patient.

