##### 8.1.4.2.2 Criteria for Discontinuing Antiretroviral therapy

At any time during treatment with antiretroviral therapy, antiretroviral medication may be discontinued for conditions described in Section 8.1.2, or for any other serious adverse event that may be related to the use of medication. In general, grade III and IV serious adverse events will result in discontinuation of one or more antiretroviral medications. For adverse events of grade I or II, antiretroviral therapy will be discontinued if the adverse event recurs when drug is re-started or when the adverse event worsens after dose adjustment.

Drug may be discontinued under the following circumstances:

- Allergic hypersensitivity reaction to study drug.
- Development of a toxicity that warrants permanent discontinuation of any study drug
- Recurrence of treatment-limiting toxicity on re-challenge will result in permanent discontinuation of the putative responsible drug.
- Confirmed virologic failure (HIV RNA > 200 copies/ml after six months of treatment) and no remaining alternatives for antiretroviral therapy (Section 8.1.3).
- Request by the subject to withdraw.
- The patient refuses further therapy.
- Failure or inability to comply with antiretroviral therapy
- Clinical reasons believed life threatening by study investigators, even if not addressed in the toxicity management of the protocol.
- Subject judged by the investigator to be at significant risk of failing to comply with the provisions of the protocol as to cause harm to self or seriously interfere with the validity of the study results.
- Termination of the study.
- Withdrawal of the study drug(s) at the request of the sponsor.
- Requirement for prohibited concomitant medications (see Table 8)

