The primary outcome for the study is HIV disease progression. This is defined as the time interval between enrollment and the development of one or more of the following endpoints, whichever occurs first: decline of CD4+ count < 250/µL, new AIDS-defining condition, or death. When a subject has met the criteria for primary outcome for CD4+ counts, the date for the first of 2 consecutive CD4+ counts will be used to mark failure time. The primary analysis of the study for each outcome will be to compare the failure-time distribution of the treated to the reference group. Separate failure-time distributions will be estimated for each treatment group using the Kaplan-Meier method78 and compared using the log-rank test.79 Stratified analysis will be performed for the primary outcome according to categories of baseline viral load.80 A Cox proportional hazards regression model81,82 will be developed to evaluate the effect of treatment on disease progression. In these analyses, the failure event will be HIV disease progression; subjects will be censored because of withdrawal during the study or at end of study. We will assess whether censoring is independent of study outcome as this is a fundamental assumption of survival analysis. In these regression models, observed event-free survival will be the dependent variable.

The basic Cox proportional hazards model for this analysis will be formulated as follows:

where h (t,X) is the observed hazard, h0 (t) is the baseline, unmeasured hazard for disease progression, β is the regression coefficient for treatment, ARV is the variable coding for immediate versus delayed ARV treatment (1 and 0, respectively), i the vector of regression coefficients for the covariates, Xi is the vector of covariates that may include time since treatment. This vector will contain known prognostic factors for HIV infection in Africa such as age, tuberculin skin test, baseline CD4+ count, hemoglobin, and performance status. This vector of covariates will also include the time period between initiating antituberculosis therapy and date of randomization to account for varying times in initiating antiretroviral therapy. The assumption of proportional hazards will be tested using graphical methods and formal statistical tests. If this assumption does not hold, then stratified Cox regression models will be developed, stratifying on the variable with non-proportional hazards.

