The hazard ratio, or relative risk, for the comparison of immediate treatment versus delayed treatment will be estimated from the Cox regression model as:

where ARV (1) codes for immediate treatment and ARV (0) for delayed treatment. The likelihood ratio test using the –2 log-likelihood for nested models will be used to assess statistical significance. Confidence intervals (95%) for the hazard ratio will be calculated using the standard error of the regression coefficient.

In any clinical trial, non-adherence with the assigned treatment poses challenges not only in the conduct of the trial but in the analysis. Adherence with study medication will be optimized through health education, frequent monitoring and modified directly observed therapy during punctuated therapy. Despite these efforts, it is possible that non-adherence will occur. Non-adherent participants will remain in the analysis to preserve the strict intention-to-treat approach. To evaluate the potential impact of non-adherence, we will perform a stratified analysis for main outcomes according to level of non-adherence, as we have done in previous clinical trials.83,84

Although random allocation of treatment would balance known and unknown confounding factors at baseline between the punctuated ARV versus the reference arm, it is possible that losses during the first 6 months of observation will alter the nature or the study groups at the beginning of this observation period. To address this potential problem, the prognostic characteristics of the intervention and reference groups will be compared at the start of the post-intervention observation period. Failure-time methods that utilize the area under the survival curve or marginal structural models will be developed to adjust for any differences between these groups after the intervention period.

Rate of change in CD4+ count according to treatment periods

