#### **10.2.2.4** **Additional Analyses**

The primary analysis as described will be performed according to the principles of intention to treat. In the event of withdrawal secondary to ineligibility, non-adherence, refusal, or toxicity, we will perform subgroup analyses of patients as treated, stratified by the degree of adherence. Propensity scores will be generated to capture the likelihood of non-adherence. Using the propensity scores, we will stratify patients according to the scores and examine the effect within and across strata. If the results of this ancillary analysis concur with the intention-to-treat analysis, then the interpretation of the results will be straightforward. If the results of this analysis differ from the intention-to-treat analysis, then the intention-to-treat analysis will be reported as the primary results because it is least likely to be biased.

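### Section 6.4 dates study-drug stops not due to an adverse reaction at study withdrawal, so patients who stop ARV but stay in follow-up get no stop date, or one that is too late

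*Protocol*

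**What the plan says.** Section 6.4 belongs to Study Outcomes, so it defines something to be analysed. Its first sentence covers stops due to an adverse drug reaction. Its second covers everything else: "Drug discontinuation for causes other than adverse drug reactions", with study withdrawal and loss to follow-up as examples and an open-ended close, "will be defined as the date the patient withdrew from the study".

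Elsewhere the protocol treats stopping drug and leaving the study as different things:

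- Section 8.1.4.1: "To discontinue study drug means to stop one, or more, study medications without the intent of restarting the medication". Leaving the study is not mentioned.
- Section 8.1.4.2.2 lists "The patient refuses further therapy" and "Failure or inability to comply with antiretroviral therapy", and also the need for a prohibited medication. A request to withdraw is a separate item in the same list.
- Section 10.2.2.1: "Non-adherent participants will remain in the analysis to preserve the strict intention-to-treat approach". The same section says that "subjects will be censored because of withdrawal during the study or at end of study".
- Section 10.2.2.4, where withdrawal follows from ineligibility, non-adherence, refusal or toxicity: "we will perform subgroup analyses of patients as treated, stratified by the degree of adherence".
- Section 8.1.2.1.2 ties documentation of grade III and IV events to study therapy and the 60 days after the last study dose.

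**The concern.** A patient who refuses further ARV, or cannot comply with it, but keeps attending visits has stopped drug without withdrawing. Section 6.4 then points to a date that is not the stop date and may never occur. Three things are at stake.

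1. The discontinuation outcome is undefined or late for these patients.
2. If treatment duration is taken from the 6.4 date, the as-treated comparison credits early stoppers with exposure they did not have.
3. Because the 6.4 rule expects a withdrawal date for each such stop, and section 10.2.2.4 describes refusal and non-adherence as causes of withdrawal, a drug stop could be entered as a study withdrawal and censored in the primary analysis. In Step 2, before an outcome, this would fall almost wholly on the punctuated arm, because section 5.1 says the anti-TB drugs are not study drugs.

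**Working it through.** The protocol gives no figure on this point, so there is none to reproduce. The check is mainly one of text.

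**Step 1. Does the rule reach patients who stay on study?** The two examples in 6.4 are exits, but the wording covers all causes other than adverse drug reactions and the list is open. Section 8.1.4.2.2 supplies at least three causes that do not require an exit: refusal of therapy, inability to comply, and prohibited medication. No other section dates them. They fall under 6.4 or have no rule.

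**Step 2. What date results?** Take a punctuated-arm patient who refuses further Trizivir at the month 2 visit.

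- If the patient stays to the end of the study, there is no withdrawal and so no 6.4 date.
- If the patient withdraws at the month 12 visit, the 6.4 date is month 12, which is 12 - 2 = 10 months late and 12 - 6 = 6 months after the planned course would have ended.
- Under section 8.1.2.1.2 the event-documentation window runs 60 days from the last dose at month 2, to about month 4. The two sections therefore rest on different dates for the same patient.

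**Step 3. How many patients?** The protocol gives no rate of stopping for such reasons. If it is 5-10% of the punctuated arm (assumption): 0.05 x 175 = 8.75, about 9; 0.10 x 175 = 17.5, about 18.

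**Step 4. Scale of the secondary risk, if it occurred.** Inputs from section 10.1: 175 per arm, reference median of 2 or 3 years, 3-year accrual, 5% dropout per year, two-sided alpha 0.05. The 5-year duration is in the synopsis. The 35% effect is read as a hazard ratio of 0.65. Assumptions added: exponential times, uniform accrual, and wrongful censoring at 3 months for 5% or 10% of the punctuated arm.

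With event hazard λ (ln 2 / median in the reference arm, 0.65 times that in the punctuated arm), dropout hazard δ = -ln 0.95 and follow-up f, the event probability is λ/(λ+δ) x [1 - exp(-(λ+δ)f)], averaged over f from 2 to 5 years. For a wrongly censored patient f is 0.25 years. Power is Φ(√(d/4) x |ln 0.65| - 1.96), with d the total number of events.

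| Reference median | Events, power with none wrongly censored | 5% censored | 10% censored |
|---|---|---|---|
| 2 years | 199.1, 86.0% | 195.2, 85.3% | 191.4, 84.6% |
| 3 years | 153.3, 76.0% | 150.4, 75.2% | 147.4, 74.4% |

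The loss is about 3-8 events and 0.7-1.6 points of power. Only the differences are used here; the starting values come from a closed form and are below the protocol's simulated 90% and 80%, a separate matter. The table does not measure bias from informative censoring in one arm, which would be the larger worry.

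**The case against.** The strongest reply is that 6.4 should be read with its examples. Both are exits from the study, and for a patient who leaves, the exit date is a reasonable proxy for the end of drug. That stands for those patients. It does not rescue the open-ended rest of the list, which has no other rule.

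Second, no analysis in section 10.2 names the 6.4 date. Adherence is captured independently by observed dosing and unscheduled pill counts (5.2.4), questionnaires at week 2 and months 1 to 6 (7.3.2) and the treatment card (11.9). This also stands. A reader might infer that a month 2 refuser will be counted as having taken the full six-month course. The documents do not show that: such a patient would appear as non-adherent in all these records. The exposure error arises only if exposure is derived from the 6.4 date.

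Third, a reader might infer that the plan censors patients who stop ARV. It does not. Section 10.2.2.1 analyses everyone as assigned whatever their adherence and keeps non-adherent patients in, and nothing tells sites to log a withdrawal when drug is stopped. What remains is that 6.4 and 10.2.2.4 blur the two events while 10.2.2.1 censors on one of them. Even then, a censored patient contributes time up to censoring and is not lost from the primary analysis.

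Finally, virologic failure is also among the reasons for stopping in 8.1.4.2.2, but it does not illustrate this point. Section 8.1.3 defines it after six months of therapy, so it cannot ordinarily shorten the six-month course.

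**Conclusion.** The point holds as a wrongly stated definition. For patients who stop ARV for a reason other than an adverse drug reaction and remain in follow-up, the 6.4 date is undefined or too late. It conflicts with the definition in 8.1.4.1, the list in 8.1.4.2.2 and the last-dose anchor in 8.1.2.1.2. The direct damage is to the discontinuation outcome and to any as-treated exposure built on it.

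The intention-to-treat analysis as written is not affected. Wrongful censoring is a coding risk that would run against section 10.2.2.1. No stated sample size, power or alpha changes. The number of patients is unknown: 9-18 of 175 rests on an assumed 5-10% stopping rate, and the small power losses rest on that rate, on censoring at 3 months and on the coding error actually happening. It is worth correcting because the rule is wrong as stated and the correction is nearly free, not because a large effect has been shown.

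**What to change.** In section 6.4, define the date of discontinuation, whatever the cause, as the date of the last dose of study drug taken, with the cause coded as a separate variable. Record study withdrawal and loss to follow-up as separate events with their own dates. State in 6.4 and 10.2.2.1 that stopping ARV alone is neither study withdrawal nor a censoring event, and reword section 10.2.2.4 so that stopping drug for non-adherence or refusal is not called withdrawal.

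The cost is a few sentences. Section 11.9 already has study-drug administration documented on the treatment card, so the last-dose date needs no new data collection. No dose, schedule or clinical rule changes.

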# 7.0 CLINICAL AND LABORATORY MEASUREMENTS

As indicated in Section 3.2, patients progress through the study in a series of Steps. This section describes the evaluations made at each Step in the study. Measurements include serial medical history and physical examination, chest X-ray, sputum microscopy and culture, urine pregnancy test, and laboratory assessment of initial metabolic, hematologic, hepatic, and renal function (see Study Follow‑up and Laboratory Testing Schedule - Appendix I). Sputum specimens will be collected using standardized procedures. Three separate Schedules of Evaluations are provided corresponding to Screening and Steps 1 (Study Entry and Initiation of standard Anti-TB therapy), Step 2 (Randomization and Study Intervention) and Step 3 (Primary Study Outcome and Delayed Antiretroviral Therapy).

Serum AST and total bilirubin should also be drawn at any time a patient is on anti-TB or antiretroviral therapy if the subject develops symptoms of hepatitis (nausea, vomiting, malaise, jaundice, or fatigue). CBC and platelet count should be repeated if there are clinical signs of anemia (pallor, hematemesis, hematochezia, etc.) or thrombocytopenia (petechiae, bruises, etc.). If a patient develops hepatotoxicity requiring study drug discontinuation, the following evaluation is suggested: patient interview with review of ethanol intake and use of any other hepatotoxic drugs such as acetaminophen, and obtain hepatitis serologies as appropriate [hepatitis A Ig M antibody (HAV IgM), hepatitis B surface antigen (HbsAg), hepatitis C antibody (HCV) Ab].

## 7.1 Screening Measurements

The following screening evaluations (Appendix I - Study Schedule, SCREENING and STEP 1) will be performed for all subjects.

1. Screening informed consent
2. Medical history and physical examination, including weight
3. Posterior-anterior chest X-ray (if not performed within the previous 14 days)
4. Confirmatory HIV testing algorithm (Appendix III)
5. Sputum semi-quantitative AFB smear and semi-quantitative culture (colony forming unit assay on solid media) X 3
6. Sputum MTB drug susceptibility testing done on these positive screening samples
7. Urine or serum -HCG pregnancy test (females of child bearing potential only)
8. CBC, differential white blood cell and platelet count
9. Serum aspartate aminotransferase (AST), serum total bilirubin
10. Serum creatinine
11. Serum glucose (for clinical management only)
12. CD4+ lymphocyte count and percent
13. Storage of two pre-treatment MTB isolates at –70 C. for later DNA RFLP genotyping

## 7.2 Step 1 – Baseline (Study Entry Measurements), Initiation of Antituberculosis therapy

### **7.2.1 Baseline Evaluation**

Patients who meet all of the inclusion and none of the exclusion criteria for study entry enter Step 1 and undergo a baseline evaluation prior to starting antituberculosis treatment. The evaluation is summarized below (see Appendix I, Step 1):

1. Informed consent
2. Medical history and physical examination, including weight
3. Plasma HIV RNA by Roche Amplicor
4. Peripheral blood mononuclear cell (PBMC) storage, 2 aliquots/ Immune Function (Flow cytometry to assess cell surface activation markers, EliSpot to assess CD4 and CD8 T cell specificity to HIV and microbial peptides, Whole blood assays to determine antigen specific response to HIV and microbial antigens)
5. Plasma & Buffy Coat storage, 5 ml.

### **7.2.2 Scheduled Visits During Step 1**

Antituberculosis therapy will be initiated following the Baseline visit. Patients will be evaluated weekly during Step 1. At Week 1 patients will first be assessed for eligibility for randomization, with exclusions based on contraindications to starting a Trizivir-based punctuated ARV therapy. Between Weeks 2 and 4, patients that are found eligible for randomization will receive treatment assignment and will progress to Step 2 at time of randomization. Patients, who do not meet criteria for randomization at Week 2, may be reassessed for eligibility for randomization at Weeks 2 or 3. The weekly evaluations will consist of (see Appendix I, Step 1):

1. Interim history and physical exam including vital signs, intercurrent illnesses, concomitant medications, adverse experiences, and major TB and HIV-related signs and symptoms (Week 1; Week 2, 3 if previous weeks results not in acceptable range for randomization; sick visits as indicated)
2. New diagnoses and/or hospitalizations since the last study visit (Week 1; Week 2, 3 if previous weeks results not in acceptable range for randomization; sick visits as indicated)
3. Adverse experiences survey (Week 1; Week 2, 3 if previous weeks results not in acceptable range for randomization; sick visits as indicated)
4. Sputum semi-quantitative AFB smear and culture on solid media (as indicated)
5. Urine or serum -HCG pregnancy test (females of child bearing potential only) (Week 1; Week 2, 3 if previous weeks results not in acceptable range for randomization; sick visits as indicated)
6. CBC with differential (Week 1; Week 2, 3 if previous weeks results not in acceptable range for randomization; sick visits as indicated)
7. Serum aspartate aminotransferase (AST), serum total bilirubin (Week 1; Week 2, 3 if previous weeks results not in acceptable range for randomization; sick visits as indicated)
8. Serum creatinine (Week 1; Week 2, 3 if previous weeks results not in acceptable range for randomization; sick visits as indicated)
9. CD4+ lymphocyte counts (as indicated)
10. Adherence questionnaire (anti-TB therapy, not done on randomization visit)
11. Disease specific diagnostic test (as indicated)
12. Quality of life assessment (Week 1)

**Laboratory values must be within acceptable range within 14 days prior to randomization.**

Patients who do not meet the criteria for randomization will remain in the study, but will not be randomized to intervention. Instead, they will be treated for active tuberculosis with antituberculosis therapy and will be followed according to evaluations described in Step 2 (see appendix I, Step 2).

## 7.3 Step 2 – Measurements during Intervention Period

### **7.3.1 Randomization Baseline-Step 2**

For patients screened and eligible for randomization, they will have a baseline randomization evaluation including:

1. Plasma HIV RNA by Roche Amplicor
2. Plasma storage, 5 ml.
3. Peripheral blood mononuclear cell (PBMC) storage, 2 aliquots/ immune function (Flow cytometry to assess cell surface activation markers, EliSpot to assess CD4 and CD8 T cell specificity to HIV and microbial peptides, Whole blood assays to determine antigen specific response to HIV and microbial antigens)

Assessments from Step 1 may be used for pre-antiretroviral baseline status if they were completed within two weeks before randomization.

### **7.3.2 Intervention Phase Study Visit**

Following treatment assignment and initiation of study intervention, patients will be evaluated one and two weeks after initiation of ARV treatment and then monthly during study intervention phase (see Appendix I, Step 2).

1. Medical history and physical examination including weight, major TB and HIV-related signs and symptoms and primary study outcomes (Week, 2, Months 1, 2, 3, 4, 5, 6, and as indicated)
2. New diagnoses and/or hospitalizations since the last study visit (Week 2, Months 1, 2, 3, 4, 5, 6, and as indicated)
3. Posterior-anterior chest X-ray (8 weeks, and between 22 and 24 weeks)
4. Adverse experiences survey (Week 2, months 1, 2, 3, 4, 5, 6, and as indicated)
5. Sputum semi-quantitative AFB smear and culture on solid media X 2 (between 4 & 6 weeks, 8 weeks, and between weeks 18 & 20 from the start of anti-TB treatment)
6. MTB drug susceptibility (as clinically indicated)
7. Urine or serum -HCG pregnancy test (females of child bearing potential only) (Week 2, Months 1, 2, 3, 4, 5, 6, and as indicated)
8. CBC, differential white blood cell and platelet count (Week 2, Months 1, 2, 3, 6, and as indicated)
9. Serum aspartate aminotransferase (AST), serum total bilirubin (Week 2, Months 1, 2, 3, 6, and as indicated)
10. Serum creatinine (as clinically indicated)
11. CD4+ lymphocyte counts (Weeks 2, Months 1, 3, 6, and as clinically indicated)
12. Plasma HIV RNA by Roche Amplicor (Weeks 2, Months 3 and 6, and as clinically indicated)
13. Adherence Questionnaire for antituberculosis and antiretroviral therapy (Week 2, Months 1, 2, 3, 4, 5, 6, and as indicated)
14. Quality of life assessment (month 6)
15. Urine INH testing (Week 2, Months 1, 2, 3, 4, 5, 6)
16. Plasma storage (Weeks 1, 2, Months 1, 2, 3 and 6)
17. PBMC storage/ immune function (Week 2, Months 3, and 6)
18. Store MTB isolate for DNA fingerprinting (All isolates from positive cultures of suspected relapse cases will be stored at -70° C for DNA finger printing with the patient’s initial isolate, as clinically indicated)
19. Disease specific diagnostic test (as clinically indicated)

